### Ethics and dissemination

This sub-study is included in the CHIPS Trial protocol, which has been reviewed and approved by Bellberry Human Research Ethics Committee (approval 2021-03-295). The CHIPS Trial is registered with the Australian New Zealand Clinical Trials Registry (ACTRN12621000751875). Findings will be presented at national/international forums and reported in peer-reviewed publications.

## Discussion

Early studies investigating the transmission of Strep A in the 1950s by Hamburger *et al*. [14, 15, 36, 37] enhanced scientific understanding of how to prevent human-to-human transmission and have been relied upon to this day – including informing the methodology of this sub-study. Notably, Hamburger and colleagues identified Strep A to have transmission potential of up to 9.5 feet (2.9 metres) in those with a symptomatic infection whilst sneezing, although very limited transmission potential was identified at any distance whilst talking [14]. The authors believe there is a benefit in contemporary replication to confirm these findings while ascertaining whether airborne or other methods of transmission may also occur. These proposed experiments capitalize on a human challenge study being conducted and provide the opportunity to increase our understanding of Strep A transmission mechanisms in the modern era.

The timing of experimentation, specifically settle plate placement and swabbing, coincides with the periods of maximal movement in the room as participants are assessed for potential symptoms of pharyngitis and have samples taken. Hence it is expected that this will be the period where transmission potential is at its highest – a study strength. While practice with HBA-CNA plates suggests exposure for no more than 4 hours at room temperature to avoid excessive contamination and degradation of the agar [38], we hypothesize that reduced movement in the room and lower room temperatures overnight will be conducive to extending exposure of these plates to 8 hours without a cover.

Lack of facilities and resources that enable strict infection control measures (such as being able to isolate participants in a single room including own bathrooms, etc.) has often been identified as a barrier to undertaking human infection/challenge studies [39]. In our study, participants are not in separate rooms but in a hospital ward-style beds, divided by curtains. One incidental benefit of our experiments would be to demonstrate whether standard infection control measures alone (without physical isolation) are adequate for prevention of Strep A transmission and thereby demonstrate the safety of similar research studies. The penicillin concentration received by the participant will need to be factored into these observations, as current practice is to deisolate those infected with Strep A after 24 hours of appropriate antimicrobial therapy.

This above point is, however, a limitation of the methodology, with contamination a possibility. Individual participants are the only ones with access to their belongings swabbed in experiment 3, so the authors believe there to be limited chance of cross-contamination between participants. As participants keep their curtains closed droplet contamination is unlikely on any plates, but potential airborne spread remains a possibility. This is also possible with the overbed plates placed at a height of 2 metres. As all participants are being given the *emm75* strain of Strep A, the only way to confirm contamination is if the samples of a participant are positive for Strep A despite no nasal or throat samples being taken from the participant confirming this. Symptomatic assessment will also be referred to should this occur.

These experiments have several limitations. Firstly, it is a small pilot study of only 20 participants due to resource and personnel constraints. However, this is the first time similar experiments have been conducted to improve our knowledge of Strep A transmission in more than 70 years. Participants receive a placebo or varying concentrations of penicillin infusion, which may reduce the likelihood of Strep A inoculating the agar settle plates or surface swabs. This limitation is overcome by inclusion of a placebo and all participants being inoculated with the same standardized dose of *emm*75. There is a possible limitation in restricting the distances in experiment 2 to 180 cm; however limitations of space in the confinement facility prevented further extension of this experiment without potentially exposing staff and other participants. Further, the CRO deemed asking challenged participants to cough or sneeze at these distances to be an unacceptable level of exposure risk to others; thus, talking was selected as an appropriate intermediary. Finally, time and resource constraints have limited the use of more specialized equipment – such as microbial air samplers – to determine the influence of factors such as airflow and air exchange rate [40] in this study, although the research team are presently investigating the possibility of employing such methods in households where the burden of Strep A is high. The results from this sub-study will of necessity precede the development of future protocols.

In conclusion, any results elicited from these experiments will be of benefit to the scientific literature in improving our knowledge of opportunities to prevent Strep A transmission as a direct component of the primordial prevention of rheumatic fever. Acute rheumatic fever remains an uncontrolled risk in low- and middle-income settings, and impoverished populations in high-income settings. New strategies for all levels of prevention are needed. Our work provides an opportunity to make important advances towards better understanding of opportunities for prevention.

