## Method and analysis

### Study design

This sub-study forms a component of the Controlled human infection for penicillin against *
Streptococcus pyogenes* (CHIPS) Trial, (registration number ACTRN12621000751875), a double-blind, placebo-controlled, randomized trial using a previously described human challenge model [31]. Briefly, the CHIPS Trial is designed to determine the optimal dose of penicillin needed to prevent Strep A pharyngitis, conducted in a purpose-built research facility resembling a hospital ward managed by a contract research organization (CRO). All potential participants undertake screening throat swabs and a serum *emm*75 type-specific serology to exclude Strep A carriage or prior infection with the same strain. Each participant is then randomized to receive one of five doses of steady-state penicillin infusions – 0 (placebo), 3, 6, 12 and 20 ng/mL – prior to receiving a direct oropharyngeal challenge with an inoculum of the *emm*75 strain of Strep A via a ‘reverse’ throat swab [32, 33]. Participants are then monitored for development of Strep A pharyngitis according to pre-specified outcome criteria during a confinement period lasting up to 6 days. All participants will be treated as possible infections. This sub-study involves three separate – but related – experiments (detailed below).

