### Study objectives

The primary objective of this sub-study within CHIPS is to assess the transmission potential of Strep A in a clinical environment, where the timing and infective dose of Strep A causing potential pharyngitis are pre-defined. Secondary objectives include determining the distance of Strep A droplet spread during conversation, investigating potential airborne spread of Strep A, and the isolation of Strep A from hard and soft surfaces in the clinical environment. It is also anticipated that this sub-study may allow for determination of the impact of different doses of treatment with penicillin against the transmission potential of Strep A.

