### Microbiological analysis

All swabs and CNA plates collected will undergo transfer and processing for microbial culture for beta-haemolytic streptococci (BHS) using gold standard culture methodology [35] and according to Clinical and Laboratory Standards Institute (CLSI) standards. If no bacterial growth is observed after 24 hours, incubation will be extended for a further 24 hours to allow growth of slow-growing or small colonies. The presence of Strep A as indicated by β-haemolytic morphology will be confirmed with subculture, bacitracin sensitivity testing and positive group A latex agglutination reaction (Streptex, Thermo Scientific). Strep A isolates will be stored at −80 °C to permit further strain characterization. Results will be reported as the presence or absence of Strep A on each sample. Quantitation of the amount of Strep A is not possible with this experimental design.

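### The contamination criterion can detect spill-over only around culture-negative participants, and a design that challenges everyone cannot show that infection control without isolation is adequate

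*Protocol article*

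**What the plan says.** All locations are in the Protocol article.

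- **Layout (Discussion).** The article says that "participants are not in separate rooms but in a hospital ward-style beds, divided by curtains".
- **Challenge (Study design).** Each participant is randomised to an infusion level "prior to receiving a direct oropharyngeal challenge with an inoculum of the" emm75 strain. No un-inoculated person is described as being sampled.
- **Contamination criterion (Discussion).** Because everyone has the same strain, "the only way to confirm contamination is if the samples of a participant are positive for Strep A despite no nasal or throat samples" from that participant confirming it. Symptoms are consulted only once this has happened.
- **Remaining route (Discussion).** With curtains closed, "droplet contamination is unlikely on any plates, but potential airborne spread remains a possibility". The plates at 2 metres are mentioned in the same context.
- **Objective (Study objectives).** One secondary objective is "investigating potential airborne spread of Strep A".
- **Outcome (Microbiological analysis).** Each sample is read as positive or negative for Strep A, without quantitation. Isolates are stored "to permit further strain characterization".
- **Analysis (Statistical analysis).** Every binary outcome is compared by dose and by diagnosed pharyngitis, to describe transmission potential in cases with and without symptoms and in non-cases.
- **Claim (Discussion).** An incidental benefit would be "to demonstrate whether standard infection control measures alone (without physical isolation) are adequate for prevention of Strep A transmission", and through this the safety of similar studies.

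**The concern.** Two things are at stake.

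The first is attribution. Spill-over from a neighbour can be recognised only around a participant with no positive nose or throat sample. Around anyone else it looks like that participant's own shedding. The chance of recognising spill-over therefore depends on infection status, which is related to the groups being compared. The criterion also gives a single label, contamination, to a result that may be the most direct evidence of airborne movement between cubicles.

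The second is the infection-control claim. Adequacy of control means that people who were not infected stay uninfected. If everyone has been inoculated, that event cannot be seen. A safety statement carried into later challenge studies would rest on something this design does not measure.

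**Working it through.** The article gives no power, error rate or calculated sample size for the sub-study, so there is no figure to reproduce. The check is mainly logical, with a short calculation for scale.

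**1. Who can be flagged.** A flag needs a positive environmental sample and no positive nose or throat sample in the same participant. Culture-positive participants can never meet the second condition. The symptom check does not widen the net, because it follows a flag. With one strain and no quantitation, nothing else in the article points to the source of a positive.

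**2. One result, three readings.** Take a positive settle plate beside a culture-negative participant.

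| Section | Reading |
|---|---|
| Study objectives | Possible evidence on airborne spread |
| Statistical analysis | Counts towards transmission potential in that participant's group |
| Discussion | Contamination |

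The article does not say which reading governs. Beside a culture-positive participant, the same spill-over gets no flag and is credited to that person.

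**3. A flag is not proof.** The flagged participant was also inoculated. Bacteria from that participant that the nose and throat swabs missed would produce the same pattern.

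**4. Onward infection.** A positive throat sample in a challenged participant is explained by the challenge. Infection acquired from a neighbour carrying the same strain would look identical. With no un-inoculated contact described, there is no one in whom onward infection could be recognised.

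**5. Scale.** Inputs: up to 20 participants (Sample size). The number m of culture-negative participants is not given, so I assume 3 to 12 of 20. Participants are treated as independent, which is optimistic on a shared ward.

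- Exact (Clopper-Pearson) two-sided 95% upper limit after zero events in m: 1 − 0.025^(1/m).
- Chance of at least one flag if true spill-over affects a proportion p of participants: 1 − (1 − p)^m, shown for an assumed p = 10%.
- Share of participants in whom spill-over cannot be flagged: 1 − m/20.

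| Culture-negative m | Cannot be flagged | Upper limit after 0 flags | Chance of ≥1 flag at p = 10% |
|---|---|---|---|
| 3 | 85% | 70.8% | 27% |
| 5 | 75% | 52.2% | 41% |
| 8 | 60% | 36.9% | 57% |
| 10 | 50% | 30.8% | 65% |
| 12 | 40% | 26.5% | 72% |
| 20 (all evaluable) | 0% | 16.8% | 88% |

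For the last row, 1 − 0.025^(1/20) = 0.168. These limits concern spill-over onto samples. They say nothing about onward infection, which step 4 shows is unobservable at any sample size.

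**The case against.** The strongest reply is that the sentence is a caveat in the limitations text, not an analysis rule. The article concedes that contamination is possible, argues that it is limited (own belongings, closed curtains), calls the infection-control result incidental and says penicillin exposure must be factored in. It also concedes that the study is small. All of that is fair and lowers the weight of the point. But the belongings and curtains arguments do not reach airborne spread, as the article itself says, and none of the concessions extends to the safety claim.

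A reader might infer more than the text supports, in four ways:

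- **That the non-case rate is forced to zero.** This would need flagged positives to be set aside. The article never says so, and Statistical analysis covers each binary outcome without exclusions. The grouping there is diagnosed pharyngitis and dose, not culture status; a participant without diagnosed pharyngitis may still be culture-positive.
- **That a large false contrast between groups can be computed from a per-plate background rate.** The article gives no such rate. The plates also differ too much to share one: those in the speaking experiment are exposed for about two minutes, the cubicle plates for 4 or 8 hours.
- **That the airborne objective is lost.** A positive 2-metre plate in a culture-positive participant's cubicle is not flagged and still informs it. Only the between-cubicle part is affected.
- **That emm typing would resolve the source.** It cannot separate participants who share one strain. It can only show that an isolate is not the challenge strain.

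**Conclusion.** The point holds in this form. The criterion can identify possible spill-over only around culture-negative participants, leaves the same spill-over around culture-positive participants unrecognised, and calls a possible between-cubicle airborne result contamination and nothing else. The word confirm is too strong. The claim of adequate infection control, and of safety for similar studies, is unsupported because the design cannot observe onward infection.

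The logical part rests only on the article's text: one strain, binary results, a shared ward and challenge of everyone. For scale, zero events in all 20 would leave an upper limit of 16.8%, and zero flags among an assumed 3 to 12 culture-negative participants would leave 70.8% to 26.5%. Those figures depend on the assumed number and on independence between participants. The size of any bias in the comparison of cases with non-cases cannot be derived from the article.

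**What to change.** - State that all positive samples stay in the analysis.
- Record bed position and which participants were confined together, if the full trial protocol does not already provide for this.
- Report positives around culture-negative participants separately, with an exact confidence interval, as possible between-cubicle detection (airborne or spill-over).
- Use that rate as an approximate sensitivity reference for the case comparison. Do not subtract it as pure background: these participants were inoculated too, swabs may miss carriage, and the denominator may be very small.
- Use emm typing of stored positives only to exclude strains other than the challenge strain.
- Say that a positive sample around a culture-negative participant suggests contamination, rather than confirms it, and that same-strain spill-over around culture-positive participants cannot be recognised.
- Withdraw the adequacy and safety claim, or limit it to environmental detection of Strep A.

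The cost is slightly more analysis, a bed record, typing of a few stored isolates and a weaker claim. Bed position is best recorded as the study runs, so this should be settled before enrolment.
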